### Exploratory outcomes

The primary exploratory outcome will be a reduction in the numeric pain rating scale (NPRS) at 3 months in the PRP group, as compared to the steroid and placebo groups. The suggested minimal clinical important difference (MCID) at the time of writing is 2 points [41] or ≥ 50% compared to placebo. Secondary outcomes will include headache frequency based on daily diaries and NPRS. Additional questionnaires completed at 2 weeks prior to injection, 1 week, 1 month, and 3 months post-injection will be the Headache Impact Test-6 (HIT-6; a valid and reliable 6-item questionnaire for assessment of the impact of headaches across different diagnostic groups of headaches [42, 43]) and the quality of life in following brain injury questionnaire (QOILIBRI). As well, participants will complete daily medication diaries tracking prn analgesic use.

### Attrition and adherence

Participants will be withdrawn from the study if there is a change in routine medications during the study period or if they do not complete study questionnaires. Daily headache diaries will be completed by all participants for the duration of the study submitted on their mobile device. In the event that daily diaries are not completed, reminders will be sent out by the study team.

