Although greater occipital nerve blockade is effective in relieving headaches and associated pain, these effects are transient, with a mean duration of pain relief of just 1 month [13]. Furthermore, the risks and complications of repeated steroid injection such as weight gain, glycemic abnormalities, tissue necrosis, and hypothalamic-pituitary-adrenal axis suppression, make it less favorable as a long-term treatment [14, 15]. Other treatments described in the literature include systemic medications (i.e., NSAIDS, anti-depressants, anti-epileptics), botulinum toxin, pulsed radiofrequency ablation, occipital nerve stimulation, and surgical decompression [16, 17]. Unfortunately, these treatments have transient and widely variable success rates, highlighting the need for new and effective therapies.

Platelet-rich plasma (PRP) is an emerging biological treatment modality containing supraphysiologic concentrations of platelets, plasma, and associated growth factors [18]. PRP has garnered widespread interest as a safe and effective treatment modality in multiple fields, including orthopedics, sports medicine, ophthalmology, neurosurgery, and plastic surgery [19]. Given its efficacy in treating numerous degenerative and inflammatory conditions, PRP has recently been highlighted as a potential treatment for peripheral neuropathies [20, 21].

PRP’s anti-inflammatory and regenerative properties, safety profile, and longer duration of effect make it an attractive therapeutic modality over conventional steroid treatment in peripheral nerve disorders. PRP augments the biological repair process through several mechanisms. Specifically, it acts to encourage local angiogenesis, augment inflammation, inhibit catabolic cytokines, recruit local stem cells and fibroblasts, and induce local manufacturing of growth factors involved in tissue repair [21, 22].

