### Data analysis

The primary outcomes for this pilot trial require descriptive statistics for recruitment, completion of primary assessment, retention, and adverse effect profiles. For exploratory outcomes, change in NPRS, HIT-6, and QOLIBRI at 1 and 3 months following intervention for patients receiving PRP compared to steroid/anesthetic and normal saline will be analyzed. A two-way mixed ANOVA test will be completed to evaluate the change in NRPS between groups. Chi-square testing will be performed to determine the relationship between basic characteristics in the three groups. For secondary outcomes, Kruskal-Wallis non-parametric analysis based on ranks will be completed correcting for multiple comparisons with Bonferroni correction. All results will be presented with 95% confidence intervals. Results will be preliminary and should be interpreted with caution due to the small sample size.

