## Discussion

GON in the post-traumatic setting is a debilitating condition without effective long-term treatment options. GON can be seen commonly following concussion, especially in cases of posterior head trauma or associated whiplash injury. PRP has been studied extensively across multiple degenerative conditions but has only recently been evaluated as a potential treatment for peripheral neuralgias. PRP has the proposed advantage of restoring normal nerve physiology and spares the use of steroids, which are associated with multiple adverse effects, especially when provided repeatedly over the long term. In addition to improved management of chronic pain, patients may experience enhanced function, quality of life, and reduced medication usage. This pilot study will provide evidence to explore whether a larger double-blinded randomized controlled trial for the treatment of GON in patients with post-traumatic headache with PRP is feasible. Feasibility will be based on successful recruitment, completion of the primary intervention, retention, and adverse events.

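### Withdrawing everyone whose routine medication changes ends follow-up on an event that treatment can influence, so the 3-month comparison may rest on a selected remainder and the retention result is lowered

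*Protocol article*

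**What the plan says.** Under Attrition and adherence the article sets a mandatory rule: "Participants will be withdrawn from the study if there is a change in routine medications during the study period". A second trigger, for questionnaires left undone, stands in the same sentence. The first trigger is not limited by drug class, direction, reason or timing. No section provides for follow-up after such a withdrawal.

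Four other statements bear on it:

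- The Discussion lists a possible benefit of treatment: "patients may experience enhanced function, quality of life, and reduced medication usage".
- The Background says of greater occipital nerve blockade that "these effects are transient, with a mean duration of pain relief of just 1 month".
- Exploratory outcomes sets the endpoint: "The primary exploratory outcome will be a reduction in the numeric pain rating scale (NPRS) at 3 months in the PRP group". The same section says "participants will complete daily medication diaries tracking prn analgesic use", so as-needed use is collected as data.
- Data analysis plans the comparison: "A two-way mixed ANOVA test will be completed to evaluate the change in NRPS between groups".

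Study design describes a single perineural injection. Primary outcomes defines retention as completion of the 3-month follow-up by at least 70% of those injected.

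**The concern.** A participant whose injection did not help may have a routine drug added or increased. One who responded well may have a routine drug reduced. Both are then removed by the rule, so exclusion after randomisation depends on something that treatment can affect. The article supplies the link itself: it expects medication use to fall with benefit, and it expects relief from the comparator type of injection to last about one month on average, well short of the 3-month endpoint.

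Once the injection has been given, leaving the study takes away no study treatment. It takes away the diary and questionnaire data up to 3 months. An analysis plan can choose how to handle the gap, but it cannot recover values that were never collected.

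Two results are exposed. The 3-month NPRS, HIT-6 and QOLIBRI contrasts may no longer compare the groups as randomised. The primary retention measure also absorbs losses that the protocol imposed and the participant did not choose.

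**Working it through.** The article gives no standard deviation, drop-out rate or medication-change rate, so there is no stated figure to reproduce. From the article: 30 participants, three equal arms (taken as 10 each), a 70% retention threshold, and this benchmark: "The suggested minimal clinical important difference (MCID) at the time of writing is 2 points". Every other input below is an assumption. Negative changes are improvements, and differences are PRP minus comparator.

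**1. Retention.** If all 30 are injected, the threshold is 0.70 × 30 = 21, so at most 9 may be lost. With other loss d and rule-based removal w, the retained proportion is p = (1 − d)(1 − w), and the chance of meeting the criterion is P(X ≥ 21) for X ~ Binomial(30, p). With d = 10%:

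| Removed by the rule | p | P(at least 21 of 30) |
|---|---|---|
| 0% | 0.90 | above 0.999 |
| 10% | 0.90 × 0.90 = 0.81 | 0.95 |
| 20% | 0.90 × 0.80 = 0.72 | 0.68 |
| 30% | 0.90 × 0.70 = 0.63 | 0.28 |

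**2. Mostly failures removed.** Assume a true change of −3 on PRP and −1 on placebo, SD 2.5. A participant improving by less than 1 point is removed with probability 0.40 (or 0.60), anyone else with probability 0.05.

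- Placebo: half improve by less than 1 point, so 0.5 × 0.40 + 0.5 × 0.05 = 22.5% are removed (32.5% at 0.60).
- PRP: the share improving by less than 1 point is 1 − Φ((−1 + 3)/2.5) = 1 − Φ(0.8) = 0.212, so 0.212 × 0.40 + 0.788 × 0.05 = 12% are removed (17% at 0.60).
- Mean change among those retained: placebo −1.45 (−1.81), PRP −3.29 (−3.48).
- Observed difference: −1.84 (−1.67) against a true −2.00.

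**3. Failures, responders, or both removed.** Assume a true change of −2 on PRP and 0 on saline, SD 2.0 to 3.0, and removal of 60% of those beyond a cut-off.

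| Who is removed | PRP removed | Saline removed | Observed difference (true −2) |
|---|---|---|---|
| Change above +0.5 (failures) | 6–12% | 24–26% | −1.62 |
| Change below −3 (responders) | 19–22% | 4–10% | −1.60 to −1.64 |
| Both | 25–34% | 28–36% | −1.30 to −1.32 |
| 20% at random | 20% | 20% | −1.98 to −2.00 |

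When both kinds are removed, attrition is almost equal between arms, yet about a third of the effect is lost: (2.0 − 1.3)/2.0 = 35%. Comparing drop-out by arm would not reveal this.

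**4. No true difference at 3 months.** Assume a month-1 change of −3 with steroid and −0.5 with PRP, correlation 0.6 between month-1 and month-3 change, SD 2.5, and removal driven by the month-1 change as in step 2. Then 12–17% of the steroid arm and 25–37% of the PRP arm are removed, and a spurious PRP advantage of about 0.10 to 0.22 points appears.

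**5. Against sampling error.** With 10 per arm and SD 2.5, the standard error of a two-arm difference is 2.5 × √(2/10) = 1.12, and the 95% half-width is about 2.3 points. The biases above run from 0.10 to 0.7 points, or roughly 0.1 to 0.6 standard errors.

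**The case against.** The strongest reply is that the rule is narrower than it first looks. It concerns routine medications only. As-needed analgesic use, the most obvious response to relief or failure, is recorded as data and triggers nothing. The Discussion's remark on lower medication use does not say that routine drugs are meant, and some routine changes will have nothing to do with headache. A reader might infer that a medication change simply is an effect of treatment and that participants are removed by outcome. The text does not support that: a change can be a consequence of outcome, and no more.

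A reader might also infer that failures leave the placebo arm and flatter it. That direction is not established. Responders may be removed too, and no rate of routine-drug change is given. The article likewise says nothing about how PRP performs at month 1, so step 4 is only an illustration.

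The contrast is exploratory, the results are declared preliminary, and the illustrated bias is small beside the sampling error of 10 per arm. This lowers the severity, but the caution in the article is about sample size and does not cover selection.

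It can fairly be said that a feasibility pilot should count what its own rules cost. That stands as a reason to leave the retention criterion alone. It does not justify reporting imposed and voluntary losses as one figure, because a larger trial needs to know which it is facing.

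Finally, one might infer that withdrawn participants drop out of adverse-event follow-up. Data management and monitoring has events reported by telephone or email and does not say that this ends at withdrawal, so the claim is not made here.

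**Conclusion.** The point holds in limited form. The rule is explicit, nothing in the article keeps these participants under observation, and 3-month values lost in this way cannot be recovered by analysis. The exploratory 3-month comparison may therefore be made in a selected remainder. The bias has unknown size and direction: about 0.1 to 0.7 NPRS points under the assumed rates, and close to none if the changes are unrelated to outcome.

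The effect on a primary measure is simpler. Any removal under the rule lowers retention, and with 10% other loss assumed, removal of 20% or 30% makes the 70% threshold uncertain or unlikely to be met. Whether removals would reach those levels cannot be told from the article.

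Severity is moderate, because no efficacy decision in the article rests on the affected contrast.

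**What to change.** In Attrition and adherence, delete withdrawal for a change in routine medication and put in its place: *Participants whose routine medication changes stay in follow-up, complete all diaries and questionnaires to 3 months, and are analysed in the arm to which they were randomised. The drug, direction, date and reason of the change are recorded.*

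Then:

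- Report medication increases and decreases by arm.
- Add one sensitivity analysis that treats an increase in headache medication as non-response.
- Keep the 70% retention criterion as written, and report any study-imposed withdrawals separately from voluntary loss. Restricting the criterion to voluntary loss would be a mistake, because it could excuse the questionnaire non-completers whom the same sentence withdraws.

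The cost is a short amendment through the ethics board, a route the article already describes, and one extra analysis. A diary field for routine drugs may be needed, since Exploratory outcomes describes the medication diary as tracking as-needed analgesics. Recruitment was still open at submission. The downside is that the main estimate then includes the effect of changed co-medication, which the recorded data and the sensitivity analysis make visible. No change to clinical care is proposed.

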**Methods:**

Thirty adults (over 18 years of age) with post-traumatic GON will be randomized into one of three groups: (1) autologous PRP injection, (2) steroid/anesthetic injection (standard care), or (3) placebo injection with normal saline. Injections will be performed to the greater occipital nerve under ultrasound guidance by a trained physician. Daily headache intensity and frequency data will be collected pre-injection and for the duration of the study period. Feasibility will be defined as greater than 30% recruitment, 70% completion of intervention, 70% retention, and less than 2 minor adverse events. Exploratory outcomes will be explored using the Headache Impact Test-6 (HIT-6, a valid and reliable 6-item questionnaire for assessment of the impact of headaches across different diagnostic groups of headaches) and the quality of life in following brain injury questionnaire (QOILIBRI).

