Multiple animal and in vitro studies have demonstrated PRP’s ability to assist in remyelination, axonal regeneration, and functional neurologic recovery in models of peripheral nerve injury [20, 23–32]. There have been few in vivo studies of PRP in treatment of peripheral neuropathies with variable success rates [33–37]. One randomized controlled trial found significant pain reductions in 60 patients with carpal tunnel syndrome and improvement of multiple markers of nerve function which persisted to 6 months following a single PRP injection [20]. Another clinical trial found significant improvement in pain following perineural PRP injections in patients with diabetic polyneuropathy [30].

These findings are encouraging as they reveal new therapeutic avenues in the management of peripheral nerve disorders. To our knowledge, PRP has not been investigated as a treatment for GON. We believe that PRP’s physiology, demonstrated efficacy, and safety profile make it an exciting and novel strategy to treat this debilitating condition. This study will investigate the feasibility of a randomized control pilot study for the treatment of GON in patients with post-traumatic headache using PRP. This pilot trial will evaluate the ability to recruit patients, retain patients throughout the protocol and the feasibility of implementing randomization using PRP for the treatment of patients suffering with GON following TBI. Our specific objectives are the following:
Evaluate the feasibility of a randomized pilot study of PRP as a treatment for patients with GON and post-traumatic headache in terms of recruitment (greater than 30%), attendance (70% intervention appointment attendance), retention (greater than 70% complete protocol), and acceptability of the protocol.Evaluate the safety profile of PRP for the treatment of GON in patients with post-traumatic headaches with less than 2 minimal adverse events.Exploratory objectives include evaluating whether patients with GON and post-traumatic headaches receiving PRP have significantly decreases pain, improved function, and quality of life, compared to patients receiving cortisone/anesthetic and normal saline injections.

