### Blinding and randomization

Each participant will be randomized following screening and enrollment in the study. Participants will be randomized (via sealed envelope) by a blinded research assistant in a 1:1 fashion to one of three treatment arms: (1) autologous PRP injection, (2) steroid/anesthetic injection (standard care), or (3) placebo injection with normal saline. All patients will undergo 60 mL blood draw on their scheduled day of injection. Whole blood samples will be prepared in the PRP group only; otherwise, they will be discarded appropriately. Syringes (3 mL each) will be prepared by a research assistant and will be covered in an opaque tape so the physician providing the injection is blinded to the type of injectate. The physician will fill out a questionnaire at the time of injection indicating their best guess of the syringe contents, which will be evaluated afterwards, to ensure adequate blinding. Unblinding will occur only in extraordinary circumstances if knowledge of the actual treatment received is deemed essential to providing further patient care.

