### Interventions

Injections will be prepared as stated below. Patients will be asked to complete a numeric pain rating scale (NPRS) immediately pre- and post-injection. Patients will be asked to refrain from use of anti-inflammatory medications for 2 weeks prior to the injection and for 2 weeks following the injection due to the possible inhibitory effect on the action of PRP. Two 3 mL syringes with 2 mL of injectate (PRP, steroid/anesthetic, or normal saline) will be prepared for each participant. Patients will be assessed at the time of injection and will receive a single injection, if experiencing unilateral symptoms only, or two injections to each greater occipital nerve, if symptoms are bilateral. Patients will be monitored for 30 min following injection for any immediate adverse reactions, such as local reaction, increased pain intensity, anaphylaxis, nausea, or dizziness.

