### Primary outcomes

The primary outcomes of this trial will assess the feasibility of a double-blinded randomized control trial for the treatment of GON in patients with post-traumatic headaches. This pilot trial is a smaller version and will aim to inform a more extensive and larger version of this randomized control trial. Specific outcomes for evaluation will include the following:
Recruitment: Ability to recruit at least 30% of those patients screened for participation.Intervention attendance: At least 70% of those patients recruited for the study will attend and participate in the primary intervention.Retention: At least 70% of those receiving the primary intervention will complete the 3-month follow-up.Adverse events: Adverse events will be minimal. No more than 1 individual will have an adverse event. Any adverse event will be minor and reversible (i.e., nausea, light headedness, temporary pain at site of injection).

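### Withdrawing participants from follow-up for a routine-medication change or incomplete questionnaires lowers the primary retention result and makes the 3-month pain comparison one of selected completers

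*Protocol article*

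**What the plan says.** All references are to the protocol article.

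- **Attrition and adherence:** the article has participants "withdrawn from the study if there is a change in routine medications during the study period or if they do not complete study questionnaires". The rule removes them from the study, not from treatment. It gives no number of questionnaires and no time point, and it states no exemption. For missed daily diaries the same section provides only reminders.
- **Blinding and randomization:** "Each participant will be randomized following screening and enrollment in the study". Withdrawals during follow-up are therefore post-randomisation.
- **Study design and Interventions:** treatment is one session, with one or both sides injected according to symptoms.
- **Primary outcomes:** retention is met if "At least 70% of those receiving the primary intervention will complete the 3-month follow-up". The objectives, at the end of Background, word it as "retention (greater than 70% complete protocol".
- **Exploratory outcomes and Data analysis:** the main exploratory outcome is NPRS at 3 months, PRP against steroid and placebo, by two-way mixed ANOVA. Results are described as preliminary.
- **Interventions:** participants are asked to "refrain from use of anti-inflammatory medications for 2 weeks prior to the injection and for 2 weeks following the injection".
- **Discussion:** lower medication use is named as a possible benefit of treatment.

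**The concern.** After a single injection session no study treatment remains to be stopped. Withdrawal from the study can then only end the diaries and questionnaires. Two things follow.

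First, retention is a primary outcome meant to inform a larger trial. A participant removed by the investigators counts as a loss in the same way as one who chose to leave. The measured percentage mixes willingness to stay with the effect of the protocol's own rule, and the pilot could miss its criterion for the second reason alone.

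Second, a medication change happens after randomisation and may itself result from how well the injection worked. Dropping such participants selects the 3-month comparison on an event related to outcome. An analysis plan can define analysis sets, but it cannot supply scores that were never collected.

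**Working it through.** The article gives no expected dropout, power calculation or SD for NPRS change, so there is no stated figure to reproduce. The rates and SDs below are assumptions, shown as ranges.

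**1. Room for losses.** The Abstract says "Thirty adults (over 18 years of age) with post-traumatic GON will be randomized into one of three groups". If all 30 are injected, 70% is 0.70 × 30 = 21 completers, so 30 − 21 = 9 losses are allowed. With 27 injected, 19 are needed and 8 losses allowed. With 21 injected (the 70% attendance minimum), 15 are needed and 6 allowed. Under the strict wording of the objectives, 22 of 30 are needed and 8 losses allowed.

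**2. Effect of the rule on the retention criterion.** Let *p* be retention without the rule and *w* the share of otherwise retained participants whom the rule removes. The number retained is X ~ Binomial(30, p(1 − w)), and the criterion is X ≥ 21. For example, p = 0.85 and w = 0.20 give 0.85 × 0.80 = 0.68 and P(X ≥ 21) = 0.494.

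| p | w = 0 | w = 10% | w = 15% | w = 20% | w = 30% |
|---|---|---|---|---|---|
| 0.80 | 0.939 | 0.681 | 0.494 | 0.316 | 0.085 |
| 0.85 | 0.990 | 0.854 | 0.692 | 0.494 | 0.162 |
| 0.90 | >0.999 | 0.955 | 0.854 | 0.681 | 0.277 |

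For p = 0.85 and w of 0, 10%, 20% and 30%, the strict criterion (22 of 30) gives 0.972, 0.741, 0.341 and 0.085. With 27 injected the values are 0.986, 0.837, 0.487 and 0.170; with 21 injected they are 0.971, 0.794, 0.471 and 0.187.

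Two limits apply to *w*. Someone who misses only the 3-month questionnaire may be a non-completer with or without the rule, so the added losses come from medication changes and from the 1-week and 1-month questionnaires. Withdrawals before injection count against attendance, not retention.

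**3. Effect on the 3-month comparison.** One possible mechanism was simulated with 1,000,000 participants per arm. Change in NPRS is normal with SD 2.0 or 2.5; the control mean is −1; the true difference is 2 points (the MCID quoted under Exploratory outcomes). Participants whose change is worse than 0 or than +1 are withdrawn with probability 0.5, 0.8 or 1.0.

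| SD | Withdrawn if change is above | Probability | Withdrawn, control / PRP | Completers' difference |
|---|---|---|---|---|
| 2.0 | +1 | 0.5 | 8% / 1% | 1.79 |
| 2.0 | 0 | 0.5 | 15% / 3% | 1.72 |
| 2.5 | 0 | 0.8 | 28% / 9% | 1.41 |
| 2.5 | 0 | 1.0 | 34% / 11% | 1.14 |

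The first and last rows are the extremes of the twelve scenarios. The shortfall is (2.00 − 1.79)/2.00 = 10% to (2.00 − 1.14)/2.00 = 43%. This shows that selection can matter; it does not predict its direction. If participants who worsened left the PRP arm while those who improved left a comparator arm, the difference would be enlarged.

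**4. The two medication provisions side by side.** Diaries start 2 weeks before injection (Measures), and the anti-inflammatory pause covers that same fortnight and the one after injection. Someone who takes an anti-inflammatory routinely and complies has arguably changed a routine medication during the study, and no exemption is stated. As-needed use is described separately, under Measures and Exploratory outcomes, so the overlap concerns routine users only.

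**The case against.** Several stronger readings are tempting, and the documents do not support them.

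- **One missed questionnaire means withdrawal.** The text does not say so; it may mean general non-completion. On the strict reading, with an assumed 90% completion at each of three post-injection questionnaires and independence between them, 0.9³ = 72.9% survive and P(at least 21 of 30) is 0.72. Independence is the harsh case: within-person correlations of 0.3, 0.5 and 0.8 give survival of 79%, 83% and 87% and probabilities of 0.92, 0.97 and above 0.99. Adding a 20% medication-change rate (0.729 × 0.8 = 58.3%) lowers the probability to 0.13, but that rate has no source in the article.
- **Comparator failures will be deleted.** Background says of nerve blockade that "these effects are transient, with a mean duration of pain relief of just 1 month". This says nothing about saline, and returning pain may lead to as-needed analgesic use, which is recorded and is not a stated trigger. The Discussion also allows for medication being reduced because of benefit.
- **The arm comparison is ruined.** It is exploratory and labelled preliminary. At an assumed SD of 2.5 with 10 per arm, the standard error of a difference is √(2 × 2.5²/10) = 1.12, larger than any shift in the simulation (at most 0.86).
- **The anti-inflammatory pause contradicts the withdrawal rule.** It does so only for routine users; for others there is no clash.

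It can also be argued that if the larger trial kept the rule, losses under it would be genuine feasibility information, since the objectives speak of completing the protocol. That has force, but only if rule-based and participant-initiated losses can be told apart, and the stated criterion pools them.

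None of this changes the main point: a participant withdrawn by rule after injection cannot complete the 3-month follow-up.

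**Conclusion.** The concern holds in this form. After injection the rule ends data collection and nothing else, so it can lower the primary retention result but not raise it. With 30 injected the margin is 9 losses. At 85% underlying retention, removing 10%, 20% or 30% takes the probability of meeting the criterion from 0.99 to 0.85, 0.49 or 0.16. The direction follows from the text; the size rests on assumed rates.

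For the exploratory NPRS comparison, the rule selects on an event that treatment plausibly affects. Both the size and the direction of that bias depend on who changes medication and why. A reader should not infer that the PRP effect will necessarily be understated, or that any single missed form leads to withdrawal. The consequence for retention carries more weight, because retention is a primary outcome.

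**What to change.** Amend Attrition and adherence along these lines: *A change in routine medication or an incomplete questionnaire is recorded as a protocol deviation. The participant stays in the study and continues diaries and questionnaires to 3 months. All available data are analysed in the allocated arm.*

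Keep retention as completion of the 3-month follow-up, as Primary outcomes defines it, and report losses by reason and by arm. Retention should not be redefined so that only withdrawn consent or lost contact counts as a loss: a reachable participant without 3-month data would then count as retained, against the stated definition.

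Reconcile the anti-inflammatory request under Interventions with the withdrawal rule, so that it is clear how a routine user who complies is handled. The clinical content of either provision is for the investigators.

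Diaries, medication records and reminders already exist, so no new data collection is needed. The cost is an ethics amendment while recruitment is under way, with a registry update and participant notification as relevant. Follow-up already lost under the present rule cannot be recovered, and some 3-month scores will reflect changed medication.
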